## 6.8 Exclusion criteria

The following are the criteria for exclusion from the study:

1. At risk of HIV infection as mentioned above in the inclusion criteria
2. Active tuberculosis or other systemic infectious process elicited by review of systems, physical examination and laboratory detection (for example detection of Hepatitis B surface antigen, or active syphilis).
3. A history of immunodeficiency, chronic illness requiring continuous or frequent medical intervention
4. Autoimmune disease by history and physical examination.
5. Hives or recurrent hives and severe eczema
6. A history of psychiatric, medical (including traditional medicine) and/or substance abuse problems during the past 6 months that the investigator believes would adversely affect the volunteer's ability to participate in the trial.
7. History of grand-mal epilepsy, or currently taking anti-epileptics
8. Received blood or blood products or immunoglobulins in the past 3 months.
9. Receiving immunosuppressive therapy such as systemic corticosteroids or cancer chemotherapy.

10. Use of experimental therapeutic agents within 30 days of study entry.
11. Reception of any live, attenuated vaccine within 60 days of study entry. Medically indicated subunit or killed vaccines (e.g., Hepatitis A or Hepatitis B) are not exclusionary but should be given at least 2 weeks before or after HIV immunization to avoid potential confusion of adverse reactions.
12. Abnormality in ECG that could indicate risk or make interpretation of vaccine effects difficult according to the study operating procedures.
13. Previously received an HIV candidate vaccine.
14. History of severe local or general reaction to vaccination defined as:
  - **Local:** Extensive, indurated redness and swelling involving most of the major circumference of the arm, not resolving within 72 hours
  - **General:** Fever  $\geq 39.5^{\circ}\text{C}$  within 48 hours; anaphylaxis; bronchospasm; laryngeal edema; collapse; convulsions or encephalopathy within 72 hours
15. Lactating mother
16. Study site employees who are involved in the protocol and may have direct access to the immunogenicity results
17. Unlikely to comply with protocol as judged by the principal investigator or his designate.

## 7 RECRUITMENT PROCEDURE

### 7.1 Recruitment in Dar es Salaam

As aforementioned, volunteers will be recruited from cohort of Police Officers' (PO's) volunteers in the on-going HIV incidence and socio-behavioral studies in Dar es Salaam. The established "core group" of about 400 PO's will be used to assist with educational activities on HIV/AIDS and HIV vaccine studies in the force as well as recruitment of the prospective 60 volunteers. The same procedures will be used that have proven to avoid coercion and social discrimination in two incidence studies in this group of policemen. Meetings at the Police stations, efforts by the "core group" of collaborators and a one to one contact, are the main modalities to reach potential volunteers. Information and briefing sessions containing general information through power point presentations about the study provide information sheets as well as the opportunity for individual questions and counseling will be offered. Volunteers are planned to be recruited from other populations (Prison Officers, general population including young adults) and this will be deemed especially necessary with recruitment of the required 15 female volunteers. Experiences from Mbeya will be shared for Dar es Salaam. The study site for the successive visits and HIV vaccinations will be at the building that houses the current HIVIS project clinic in Dar es Salaam.

### 7.2 Recruitment in Mbeya

Volunteers will be recruited from the Mbeya urban environment through advertisement using poster, newspaper advertisement and flyers. MMRP has developed over the years throughout the past cohort studies a well-established relationship to the communities. Community leaders and community advisory boards of various areas in the Mbeya region will help in the advertising and recruiting process. Recruitment of the required number of female participants is not considered to be a problem in Mbeya as most study participants in past studies were females (e.g. 60% in RV172). Interested volunteers will be invited to an information and briefing session. These sessions will contain general information through power point presentations about the study. Information sheets as well as the opportunity for individual questions and counseling will be provided. There will also be time for questions on an individual basis without ties to the particular group involved. Interested volunteers will receive an appointment for the first screening visit or contact details for later screening assignment. Information sessions will also be provided for the community leaders and the community advisory board. The briefing and information sessions will take place at the MMRP vaccine trial location in Mbeya.

## 8 STUDY PROCEDURES

An overview on study procedures are provided in the Study Timetable (**Appendix 1**), in the Visit Schedule and Forms Flow (**Appendix 2**) and in the Lab Schedule Flow (**Appendix 3**).

### 8.1 Screening I (Study Visit 1, 4-8 weeks before enrolment)

#### 8.1.1 Informed consent procedures and study information

The first screening visit (study visit 1) will take place between 4 and 8 weeks before the first planned injection. At this visit the study volunteer will meet the study doctor(s) and study nurse(s), and the trial will be discussed in detail associated with thorough informed consent procedures (**see Appendix 4 A or B**). This discussion will also address on the following: the meaning of 'randomization', potential adverse effects of the vaccine, and about the fact that it is unknown whether or not the study vaccines will protect or even increase the risk for him/her to acquire HIV infection. They will be informed that following immunization they may develop antibodies that will produce a positive reaction in a routine HIV test, but that provisions have been made to distinguish between a post vaccination response and HIV infection during and after the trial. This includes that volunteer will be excluded from donating blood or organs and that they may be vulnerable to social risk if they develop HIV antibodies, or by revealing their participation in the study. They will be assured of the level of care that will be made available to them should they be found to be HIV infected at any time during their participation in the study, including the screening period (see also section 17.1). HIV infections occurring after the study and observation period will be handled in the regular established HIV clinic in the police force or community as applicable. The placebo concept will also be explained. Study Participants who have received and signed the initial informed consent (Version 2.0, September 2009) will receive written information regarding the changed visit schedule. Signed and dated informed consent will be requested (**see Appendix 4 C and D**).

Volunteers will be counseled by study personnel about safer sex. They will be counseled on the importance of contraception from starting immunization up to 3 months after the last immunization and that they should continue to use condoms with sexual partners whose HIV status is not known. They will also be reminded about these items on each day of immunization. High quality hypoallergenic condoms will be provided free of charge to volunteers throughout the trial.

Upon this information about the trial and the informed consent procedures, consenting volunteers will be requested to successfully pass a test of understanding (**Appendix 5, CRF 1-I**) with at least 90% of correct answers with the possibility of maximum 3 repeated attempts.

Demographic data and participant's contact information will be collected and recorded (CRF 5-I).

#### 8.1.2 HIV counseling and testing

Study personnel will assess volunteers for past and current risk of HIV infection using the Risk Assessment Questionnaire (**Appendix 6, CRF 1-II**), followed by counseling for those who will consent to undergo HIV test prior to collecting blood. The counseling process will ensure that volunteers have sufficient knowledge about HIV infection to understand what the test is for, the implications of a positive, negative and equivocal result and the standard of care available for HIV infection locally. They will also be informed on how and when they will receive the result.

#### 8.1.3 Clinical history and examination

The clinical contact will be documented by using the Screening Visit Contact Form (**CRF 2-I**) and Screening I Physical Examination Form (**CRF 3-I**). The clinical contact will include a complete physical examination and medical history, including any ongoing medication and

any previous allergic reactions, any previous reaction to vaccination, history of epileptic fit, exposure to smallpox vaccine, and smoking practices. The general examination will include weight (kg), height (cm), mouth and throat inspection, palpation of lymph nodes (cervical, clavicles, and axillaries), blood pressure, and inspection of the skin to exclude severe eczema and check for the presence of a vaccinia vaccination scar, respiratory, cardiovascular, genital urinary, central nervous system and gastrointestinal system examination. A genital infection screening will be performed if indicated on the account of risk and symptoms according to trial specific clinical standardized operating procedures: urethral, vaginal, cervical specimens, as appropriate for common sexually transmitted infections. The medical history should ensure good general health and the absence of any chronic medical condition that could influence the safety evaluation. Relevant past and current medical conditions during the entire screening period will be documented on the Previous Condition Form (**CRF 4-II**) and current or ongoing medication documented on the Concomitant Medication Form (**CRF 4-I**).

#### **8.1.4 Safety laboratory tests and HIV testing**

All so far eligible (with among other things, at least 1 negative HIV Antibody test result within previous 3 months) volunteers will have their blood sample screened for HIV. HIV antigen and antibody ELISA will be used for initial testing. Non-reactive samples on the first ELISA will be regarded as negative. All reactive samples will be tested in duplicate on a second ELISA. Discrepant results between two ELISA's will be resolved by Western Blot and HIV RNA PCR methods (**see Appendix 7**). HIV results throughout the study will be reported to the clinic from the laboratory as infected or not infected without providing the test methods as false positive HIV ELISA or rapid test result could indicate a participants randomization to the vaccine Group (**CRF 9-I**).

Safety laboratory test will include the status of the liver (serum alanine aminotransferase and bilirubin), renal function (serum creatinine) and random blood glucose that will be followed by fasting blood sugar during screening visit 2 for individuals whose tests will be suspicious of diabetes mellitus (**CRF 9-V**). Other tests will include a complete blood count with 5 part differentials (**CRF 9-IV**) and screening for syphilis, hepatitis B (surface antigen) infection (**CRF 9-VI**) as well as urine dipsticks (**CRF 9- VII**). All women will have a urine pregnancy test done (**CRF 9-II**).

#### **8.1.5 Blood and urine collection**

Blood will be collected using a sterile needle, usually from the ante-cubital fossa, according to the SOP's and the visit schedule and transported to the appropriate laboratories. Urine will be collected into a sterile container and tested by a member of the clinical team according to trial specific SOP's. Urine dipsticks and pregnancy test will be performed at the clinic. If urine dipsticks indicate abnormal results ( $\geq 1+$ ) urine will be transferred to the labs for microscopic examination and if indicated for culture and sensitivity. The volunteer will as well be reviewed to rule out other systemic conditions that can result into abnormal urine results such as proteinuria. In cases with confirmed proteinuria of unclear etiology a quantitative/qualitative urine protein investigation can be ordered at the referral laboratories in Dar es Salaam. Determination of Protein/Creatinine Ratio by comparing the concentration of protein in the urine to the creatinine\_level in a spot urine sample may be performed and in so doing a Protein:creatinine ratio  $>45$  mg/mmol would be considered to indicate presence of proteinuria. It should be noted that the provision of expedited cold chain transport of samples for not available lab investigations from Mbeya to Dar es Salaam is possible.

All samples for routine hematology, clinical chemistry and other investigations will be labeled appropriately with the full study volunteer identity. Samples that will be analyzed after freezing shall be prepared, labeled, and stored at the appropriate temperature. Specimens that are shipped will be correctly prepared, labeled, and kept at the correct temperature.

The total estimated volume of blood to be collected at different time points is shown on the investigations flow chart for each scheduled visit (**see Appendix 3**). All biological samples to

be analyzed by the research laboratory will be collected and processed according to institutional guidelines and regulations regarding biobanks. All samples sent to the appropriate laboratories at MUHAS and MMRP will be labeled appropriately.

#### **8.1.6 Labeling procedures**

Scheduled study visits will be numbered 01, 02, etc. with the addition A-Z for post vaccination visits (e.g. 03A, 03B etc.) and J-Z for unscheduled visit (e.g. 03J, 03K etc.). Site and participant code number will contain 4 digitals indicating the first digital 3 for Dar es Salaam and 2 for Mbeya followed by 3 digitals for participant identification (e.g. Dar: No. 3001, Mbeya: No. 2001). Laboratory samples labels will contain the study visit number, the site and participant code, the date and time of collection, the type of sample (serum, plasma, blood etc.) and a unique sample identification number assigned by the site laboratory.

### **8.2 Screening II (Study Visit 2, 2-4 weeks before enrolment)**

The second screening visit (study visit 2) takes place two to four weeks before the first planned injection. This visit will include review of informed consent, inclusion criteria, medical conditions and laboratory results. Reassurance has to be made that the study volunteer fully understands the concept of the study. Volunteers will also be reminded that they are free to end all obligations in the study whenever they wish and that a premature termination will not have any negative influence in future contacts with the clinic. Available HIV results will be discussed during post-test counseling by the nursing staff, consent process reviewed and volunteers probed for questions/concerns before referral to the medical officer. The medical officer will review the informed consent process, questions/answers, review of health and concomitant medications since last visit with the volunteer as well as check inclusion/exclusion and eligibility criteria (**CRF 2-I, CRF 3-II**). An ECG will be performed for baseline assessment (**CRF9-III**) if not done at Visit 1. A competent study physician will do the interpretation of ECG results and furthermore all ECG tracings will be sent as a PDF for interpretation/approval to a cardiologist panel. If a volunteer is found to be not eligible, a Screening Outcome Form (**CRF 5-IV**) will be filled indicating reasons for ineligibility. In the case of HIV positive test results or other medical conditions leading to ineligibility volunteers will receive medical advice and/or indication concerning the referral to appropriate health facilities outside the study premises. Minor or curable medical conditions identified during the first or current screening visit which do not necessarily lead to ineligibility are subject for care and treatment provided by the study site. This might include the control of selected lab results or medical conditions as indicated by the investigator. Additional screening visits to follow-up on such medical conditions might be necessary. If more than 3 months have elapsed since Visit 1 baseline, lab examinations (CBC and chemistry) as well as a medical status examination will have to be repeated. The latest visit should be 2-4 weeks before study visit 3, with an HIV serology no older than 8 weeks. Volunteers found to be eligible throughout the screening process will be asked to provide blood for baseline immunology tests as indicated in the Lab Schedule Flow and will then receive an appointment for the enrolment and first vaccination at the study visit 3.

### **8.3 Enrolment and Vaccination I (1st DNA/Placebo) (Study Visit 3, week 0)**

The study volunteer again meets both study nurse(s) and study doctor(s) (**CRF 2-II**). Confirmation has to be made and recorded that the volunteer fulfils all inclusion/exclusion criteria including laboratory results (**CRF 5-II**) and eligibility criteria (**CRF 5-III**). If a volunteer is not found to be eligible a Screening Outcome Form (**CRF 5-IV**) will be filled indicating reasons for ineligibility. Enough time has to be planned for the visit so that all questions from the volunteer about the study can be answered or reflected upon. A senior Physician will confirm if the volunteer understands the concepts of the study and will also assess the willingness and voluntariness the study volunteer. As indicated during the informed consent procedure the volunteer had consented on a study photo identification card produced and provided by the site. This photo ID will be kept by the study participant and will have to be

presented at each study clinic contact for identification purposes, unless other unequivocal identification can be documented.

For enrolment the initial screening number will be used as the study number. This means that study numbers may be discontinuous. The participant will then be randomized into one of the study Groups.

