### **8.3.1 Randomization procedure**

Sixty plain envelopes numbered from 1 to 60 for each site are provided by the Swedish Institute for Infectious Disease Control which is responsible for the vaccine/placebo product supply. They will be divided in 6 sets of 10 envelopes. Each set will contain 3 assignments to Group IA, 3 to Group IIA and 3 to Group IIIA and 1 to either of Group IB, IIB or IIIB. Group numbers refer to the immunization schedule. The study Pharmacist will take the prepared envelopes and put them in a box that is kept under lock. The pharmacist will randomize participants accepted into the study by selecting the next consecutive envelope containing the vaccine or placebo assignment in accordance with the generated randomization list. This will be documented in **CRF 8-I** pharmacy copy. The Pharmacist will then inform the Study Nurse/medical officer at the clinic of the randomization group of the volunteer (2x versus 5x i.d. DNA priming) on the **CRF 8-II** clinical copy, including the number of the envelope, but will not inform on whether this is vaccine or placebo. The Study Nurse will record the envelope number and the group assignment (2x versus 5x i.d. DNA priming) into a register book, the medical record file (source document), as well as the outer cover of the participant's file.

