### **8.3.3 Vaccination**

Prior to the first vaccination the enrolled study participant will receive an abbreviated risk assessment and risk behavior counseling as well as pre HIV test counseling prior to HIV testing. Vital signs will be recorded and blood will be donated according to the visit schedule (safety laboratory tests, urine dip stick, HIV test, CD4 count and baseline immunogenicity tests) including pre vaccination pregnancy test from urine for female participants. The participants will then attend the medical officer who will evaluate the pre vaccination medical status (**CRF 3-II**).

A pregnancy test for female participants before each vaccination will have to show negative results *before* vaccination.

After confirming the medical eligibility for vaccine administration including a negative pregnancy test for female participants the vaccine request form (**CRF 10-II**) will be filled by the medical officer, transferred to the pharmacist who will then deliver to the nurse the appropriate vaccine/placebo that corresponds to the assigned group. The participant will then receive the first injection. After vaccination the participants will be observed for 30 minutes at the clinic for potential early adverse reactions (anaphylactic reactions). Follow-up and safety procedures as well as distribution and handling of diary cards will be performed. A detailed description of the post vaccination procedures is provided in the protocol section **Immunization** further below.

The participant will then be compensated and assigned to his next scheduled visit.

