## 9.3 Vaccination procedures and safety follow-up after immunization

The immunizations will take place in an outpatient setting. Participants will receive a baseline medical status check up including vital signs assessment to confirm on the medical eligibility before vaccine administration. Results will be documented in the appropriate CRF forms (**CRF 3-II, CRF 10-I**). Safety lab procedures, urine analysis as well as HIV testing will be performed before vaccine administration according to the visit schedule. A pregnancy test for female participants before each vaccination will have to show negative results vaccination. The pregnancy test for female participants before each vaccination will have to show negative results *before* vaccination. A vaccine request form (**CRF 10-II**) indicating the study visit number, the site and participant code, the date as well as the immunization number and immunization Group will be filled then by the study medical officer and transferred to the study pharmacist, who will deliver to the nurse the appropriate vaccine/placebo corresponding to the assigned study group. After each immunization participants will be closely observed at the clinic for 30 minutes. Vital signs and any local or systemic reaction will then be recorded and participants will be seen briefly by the medical officer to document the post vaccination status (**CRF 3-II, CRF 10-I** - this record will be indicated in the CRF with the visit number plus A). The needles, syringes and other materials will be disposed according to MNH /MMRP biohazard regulations. As with any parenteral vaccine, epinephrine and corticosteroids will be available for immediate use should an immediate hypersensitivity reaction, such as anaphylaxis, occur. Intravenous injections of vaccines will NOT be performed. Study vaccine will not be administered to individuals with hypersensitivity to any component of the vaccine. All immediate hypersensitivity reactions will be managed according to the developed SOP's. Volunteers will be contacted by phone, home visit or clinical contact at the first day following immunization for a brief adverse reaction interview. Additionally, volunteers will complete diaries over events for the evening of the vaccination day and the 7 days following each vaccination. A diary card (*see Appendix 8*) will be provided after each vaccination schedule, with instructions and a full verbal explanation for volunteers to record local and systemic adverse events following immunization, as well as any medication taken. A folder with diary cards, disposable thermometers and a ruler will be issued to each volunteer. The clinical team will provide contact information as well as a telephone numbers to call 24 hours, in order to assure contact with the study personnel if needed.

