### **20.2 Statistical analysis**

The final analysis will be conducted once all study participants have received all their immunizations and completed the 84 weeks follow-up period, or have permanently withdrawn from the study. Safety analyses will further be updated in the event that there is 108 weeks follow up. Analyses will be based on the principle of intention-to-treat. Interim analysis of safety and immunogenicity may be performed if measures are taken to maintain blinding.

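### At Visit 3 the envelope is opened and the clinic learns 2x or 5x before the Day-0 checks that clear the volunteer for the first injection

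*Protocol*

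**What the plan says.** Section 8.3 opens Visit 3 with a formal eligibility step: "Confirmation has to be made and recorded that the volunteer fulfils all inclusion/exclusion criteria including laboratory results". A Screening Outcome Form is completed for anyone who fails. The section ends with "The participant will then be randomized into one of the study Groups".

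Section 8.3.1 covers the envelopes: "The pharmacist will randomize participants accepted into the study by selecting the next consecutive envelope". Disclosure follows at once: "The Pharmacist will then inform the Study Nurse/medical officer at the clinic of the randomization group of the volunteer". What is disclosed is 2x versus 5x intradermal priming, not vaccine versus placebo. Section 6.1 states that the group is not blinded.

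Section 8.3.3 then describes what happens to someone already enrolled: "Prior to the first vaccination the enrolled study participant will receive an abbreviated risk assessment and risk behavior counseling". Vital signs, bloods, the HIV test and the pregnancy test follow. After that, "The participants will then attend the medical officer who will evaluate the pre vaccination medical status". The vaccine is requested once medical eligibility and a negative pregnancy test are confirmed. Section 9.3 says of the request form: "as well as the immunization number and immunization Group will be filled then by the study medical officer". Section 10.3 makes clear that the group on that form means 2x or 5x.

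On analysis, section 20.2 says: "Analyses will be based on the principle of intention-to-treat". Section 8.22 limits the safety analysis to people with at least one immunization.

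**The concern.** Concealing the allocation protects the comparison only until the envelope is opened. Any later discretionary step that decides who receives the first injection can differ between arms if the person deciding knows the arm. Here that person knows 2x or 5x. This split separates groups I and II from group III, which is the sizing contrast in section 20 and the reactogenicity comparison in section 20.1. A volunteer who learns of five injections may also decline at this point. Section 4.8 itself calls the five-injection procedure cumbersome.

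There is also a practical cost. A volunteer held back after the envelope is opened has used an assignment without being vaccinated. Such a person lies outside the safety analysis and has no stated place in the immunogenicity analysis.

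**Working it through.** **1. Order of events at Visit 3, as written**

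| Step | Section | Group known to clinic? |
|---|---|---|
| Inclusion/exclusion confirmed and recorded | 8.3 | No |
| Randomised; envelope opened; clinic told 2x/5x | 8.3, 8.3.1 | From here on, yes |
| Risk assessment, HIV test, pregnancy test, medical officer's evaluation | 8.3.3 | Yes |
| Vaccine request form, carrying the group | 8.3.3, 9.3, 10.3 | Yes |

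The Day-0 pregnancy test is a real gate. In Appendix 2 the only earlier scheduled pregnancy test is at Visit 1, 4 to 8 weeks before enrolment.

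**2. Envelope count (8.3.1)**

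- Active: 2 sites × 6 sets × 3 = 36 per group.
- Placebo: 2 × 6 × 1 = 12.
- Total: 3 × 36 + 12 = 120, exactly the target. No spare envelope or re-use rule is described.

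**3. The plan's sample size (section 20)**

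Inputs: 100% responders in IIIA, 80% in the comparison group, one-sided 5%, power 80%. With mean proportion 0.9:

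n′ = [1.645·√(2·0.9·0.1) + 0.842·√(0 + 0.8·0.2)]² / 0.2² = (0.698 + 0.337)² / 0.04 ≈ 26.8

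With continuity correction: n = (26.8/4)·[1 + √(1 + 4/(26.8·0.2))]² ≈ 36.1. The stated 36 is reproduced (37 if rounded up).

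**4. Exact power with the planned test (Fisher, section 20.5), one-sided 5%**

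With 36/36 responders in IIIA, the test rejects when the comparison group has at most 31/36 (p = 0.027; at 32, p = 0.057). Power = P(Bin(36, 0.8) ≤ 31) = 87.3%.

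Now suppose one volunteer is randomised but unvaccinated. This is an illustration only. With 35/36 responders in IIIA the rejection limit falls to 29 (p = 0.028; at 30, p = 0.053).

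| Scenario | Calculation | Rejection probability |
|---|---|---|
| None | P(Bin(36, 0.8) ≤ 31) | 87.3% |
| One per group, counted as non-responder | P(Bin(35, 0.8) ≤ 29) | 72.8% |
| One in IIIA only, counted as non-responder | P(Bin(36, 0.8) ≤ 29) | 59.9% |
| One in comparison group only, counted as non-responder | P(Bin(35, 0.8) ≤ 31) | 93.9% |
| One per group, left out (35 vs 35) | P(Bin(35, 0.8) ≤ 30) | 85.7% |

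With two per group, power is 70.0% if they are counted and 83.8% if left out. With three it is 50.0% and 81.8%.

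**The case against.** A reader might infer that eligibility itself is decided after allocation. The documents do not support this. Section 8.3 requires all criteria, including laboratory results, to be confirmed first, and 8.3.1 randomises only people already accepted. What follows is clearance for injection, a check repeated at every vaccination.

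The discretionary part is narrow. A pregnancy test is objective, so knowing the group cannot bias its result. Section 8.3.3 gives no stop rule for the abbreviated risk assessment, and new HIV risk is not among the withdrawal criteria in 16.1. What remains is the officer's medical judgement and the volunteer's own willingness.

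Subsection order is also imperfect evidence of timing, since 8.3.2 has syringes handed over before 8.3.3 has them requested. However, 8.3 places randomisation straight after eligibility confirmation, 8.3.1 attaches disclosure to randomisation, and 8.3.3 begins with someone already enrolled. A site following the text would open the envelope first.

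A reader might call the lost assignments irreplaceable. Section 8.22 allows replacement of people who withdraw while enrolment is open. The gap is smaller: that rule speaks of withdrawal, not of someone held back on Day 0, and no envelope is provided for a replacement.

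Finally, the fall to 73% might be read as the cost of the visit order. It depends on an analysis rule the protocol does not state and an SAP may settle. It also reflects the sizing assumption of exactly 100% response in IIIA, under which any single non-responder there has the same effect.

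**Conclusion.** The point holds as a sequencing flaw. Group disclosure precedes the last go/no-go before first vaccination, and anyone stopped there is randomised but unvaccinated, with no stated handling of the envelope or the analysis.

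The size cannot be fixed from the document. No Day-0 failure rate is given. The nearest figure is in section 4.6.1: of 60 volunteers enrolled in the earlier Dar es Salaam trial, 59 received all three DNA/placebo doses, so at most 1/60 = 1.7% were lost for any cause by then. That was a different population. The power effect also depends on which arm is affected and how such people are counted. If they are left out, power stays above the planned 80% with up to three per group, although the comparison is then no longer strictly intention-to-treat.

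The stronger argument for change is therefore not power. An analysis rule can limit the power loss, but it cannot undo a decision taken with the arm known. Vaccine/placebo blinding and the comparison of I with II are not affected, because both of those groups are 2x.

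**What to change.** Amend 8.3, 8.3.1 and 8.3.3, and 9.3 for the first injection only, to this order:

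1. Complete the Day-0 checks already planned.
2. The medical officer signs the first vaccine request without a group.
3. On receiving it, the pharmacist opens the next envelope, enters the group and tells the clinic 2x or 5x.

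Bring 10.3 into line, since it has the study nurse complete the same form with the group. Add a sentence on what happens to the envelope, and to the analysis, when someone is randomised but not vaccinated.

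No procedure is added and the sample size is unchanged. The cost is one line on a form and a short wait while syringes are prepared. Later go/no-go decisions will still be made with the group known, because the group is open by design.
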